#### Primary endpoint

The primary endpoint is the change from baseline in eGFR at Day 90, comparing pooled RMC-035 dose groups to placebo.

In the clinical routine, eGFR is the gold standard for assessment of renal function. It is also an endpoint for irreversible loss of kidney function, a diagnostic marker of CKD, and on the direct path to ESRD [13, 14]. Moreover, a permanent eGFR decline has significant prognostic implications, leading to long-term adverse outcomes on individual patient health, including elevated risk for cardiovascular events, ESRD, and mortality [15–17].

#### Key secondary endpoints

Secondary endpoints of this study include change from baseline in eGFR at Day 90, MAKE_90_, and individual components of MAKE_90_. These endpoints will be assessed using both pooled analyses and dose-level comparisons against placebo.

#### Other secondary endpoints

Other secondary endpoints are based upon pooled, and by dose strength, comparisons ofOccurrence of MAKE_60_ and each MAKE_60_ componentChange from baseline in eGFR at Day 7 and Day 60Change from baseline in SCr and CysC until Day 7Occurrence of AKI based on SCr until Day 4; this includes assessment of AKI stage per KDIGO guideline [10]Presence, titre, and cross-reactivity with endogenous A1M, of ADAs at baseline, Day 7, Day 60, and Day 90Characteristics of ADA with regards to neutralizing activity and isotype

#### Exploratory endpoints

Changes from baseline in concentrations of markers of complement activation, neutrophil activation, cytokine release and mast cell activation and plasma-concentrations of RMC-035 (area under the curve [AUC], maximum concentration [C_max_] and trough levels [C_trough_]) will be assessed.

#### Safety endpoints

The assessment of safety includes pooled, and by dose strength, comparisons ofNature, frequency and severity of treatment emergent adverse events (TEAE); a TEAE is any adverse event (AE) that occurs after start of first administration of IMP and through 72 h (inclusive) after the end of the final administration of IMPNature, frequency and severity of post-treatment AEs (PTAEs); a PTAE is any AE that occurs later than 72 h after the end of the final administration of IMPFrequency and severity of TEAEs suggestive of infusion related reactionsLaboratory test (serum chemistry, haematology and liver function) values and changes from baselineVital signs (blood pressure, pulse rate, respiratory rate, and oxygen saturation), and electrocardiogram (ECG) values and changes from baseline

### Participant timeline {13}

The study consists of 8 visits for each participant, and has three study periods:Visit 1: Screening period of 30 days (Day −30 to Day −1)◦ Day −1, the day before surgery, is a required study timepoint for randomisation and sampling of first baseline SCrVisits 2 to 6: Treatment and hospital stay period of approximately 7 days (Day 1 to Day 7)◦ Day 1 before the patient is prepared for surgery is the required timepoint for sampling of second baseline SCr◦ Treatment with study drug occurs on Day 1 at 0 and 6 h, and Day 2 at 24 h◦ Hospital stay continues until discharge at approximately Day 7Visits 7 and 8: Follow-up period until Day 90 (from discharge to Day 90)◦ First follow up visit at 60 days after surgery◦ Second and last follow up visit at 90 days after surgery

During the course of the study, visits and assessments will be performed as visualised in the study flow chart [Fig. 1] and as defined in the schedule of assessments for the full study period [Table 3] and for Days 1 and 2 [Table 4].

**Fig. 1 Fig1:**
[figure not shown]
Study flowchart*. *AE: adverse event; D: day; ICU: intensive care unit; SAE: serious adverse event

**Table 3 Tab3:** Schedule of assessments (Days 1 and 2)

		**Visit 2/Day 1** (Day of surgery)					**Visit 3/Day 2** (EOT)			
**Timepoint**	Pre-0	0	1 h	2 h	Pre-6 h	6 h	Pre-24 h	24 h	25 h	26 h
Pregnancy test	(x)									
Safety labs							x			
SCr *(local lab)*					x		x			
SCr & CysC *(central lab)*	x^1^				x		x			
12-lead ECG							x			
Vital signs	x						x			
IMP administration		x				x		x		
PK *(central lab)*	x		x	x	x		x		x	x
Biomarkers *(central lab)*	x		x		x		x		x	
ADA *(central lab)*	x									
Surgery assessment		During surgery								
RRT recording					As occurs after surgery					
Concomitant Medication recording		As occurs throughout period								
AE/SAE recording		As occurs throughout period								

*ADA* antidrug antibodies, *AE* adverse event, *CysC* cystatin C, *ECG* electrocardiogram, *EOT* end of treatment, *IMP* investigational medicinal product, *SAE* serious adverse event, *PK* pharmacokinetics, *RRT* renal replacement therapy, *SCr* serum creatinine

**Table 4 Tab4:** Schedule of assessments (full study period)

	**Screening**	**Treatment and hospital stay**					**Follow up**	
**Visit Number** (specification)	**1**	**2** (Day of surgery)	**3** (EOT)	**4**	**5**	**6** (Discharge)	**7**	**8** (EOS)
**Visit Day** (timepoint)	−30 to** −1**	**1**	**2** (24 h)	**3** (48 h)	**4** (72 h)	**7**	**60**	**90**
Informed consent	x							
Eligibility check	x							
Medical & surgical history, incl. substance use	x							
Demographics	x							
Physical examination	x			x				
Weight and (screening only) height	x						x	x
Pregnancy test (WOCBP only)	x	(x)						
Safety lab tests *(local lab)*	x		x	x	(x)	(x)		
SCr test *(local lab)*	x	x	x	x	x	x		
SCr & CysC test *(central lab)*	x	x	x	x	x	x	x,x	x,x
Randomisation	x							
12-lead ECG	x		x	x				
Vital signs	x	x	x	x				
IMP administration		x	x					
PK test *(central lab)*		x	x	**x**				
Biomarkers test *(central lab)*		x	x	x				
ADA test *(central lab)*		x				x	x	x
Surgery assessments		x						
RRT		As occurs after surgery to EOS						
Concomitant medication		As occurs from Day 1 to EOS						
AE recording		As occurs from first dose to discharge						
SAE recording		As occurs from first dose to EOS						

*ADA* antidrug antibodies, *AE* adverse event, *CysC* cystatin C, *ECG* electrocardiogram, *EOS* end of study, *EOT* end of treatment, *IMP* investigational medicinal product, *SAE* serious adverse event, *PK* pharmacokinetics, *RRT* renal replacement therapy, *SCr* serum creatinine, *SoA* schedule of assessment, *WOCBP* woman of childbearing potential

### Sample size {14}

A total of 161 participants will be randomised in a 2:2:3 ratio across three study arms: 46 for RMC-035 low dose, 46 for RMC-035 high dose, and 69 for placebo.

This design aims to achieve at least 80% power to detect a significant effect of pooled dose levels compared to placebo at a 10% two-sided significance level, assuming a treatment effect of 5 mL/min/1.73m^2^ and a standard deviation of 12 mL/min/1.73m^2^. The expected effect size is conservatively based on observations from the AKITA study in the subgroup with eGFR < 60 mL/min/1.73m^2^, where a lower starting dose was administered [8]. In this subgroup, descriptive analysis indicated a difference in eGFR of 6.5 mL/min/1.73m^2^, while a mixed model of repeated measures (MMRM) showed 7.9 mL/min/1.73m^2^. The standard deviation was derived from the AKITA study, which reported approximately 13 mL/min/1.73m^2^. To minimise variability, double assessment of centrally sampled serum creatinine at baseline, days 60 and 90 will be used for eGFR calculation, with an expected standard deviation of 12 mL/min/1.73m^2^ in the current study. A 10% drop-out rate is anticipated for the 90-day assessment, along with a 5% information loss.

### Recruitment {15}

Participants will be recruited from the pool of patients being scheduled for relevant open-heart procedures at the selected study sites. Study sites were mainly selected based upon enrolment experience in the previous phase 2 AKITA study.

## Assignment of interventions: allocation

### Sequence generation {16a}

Participants are randomised block wise in a 2:2:3 ratio to RMC-035 high dose, RMC low dose, and placebo, respectively. Stratification for eGFR (≥ 60 and < 60 mL/min/1.73m^2^) will be implemented, and at least 30% of participants will be included in the < 60 mL/min/1.73m^2^ stratum.

### Concealment mechanism {16b}

Stratified randomisation to IMP is done centrally using an interactive response technology (IRT) based upon patient information entered by the study site staff: age, gender and SCr. Blinded study site staff does not become aware of the intervention assignment.

### Implementation {16c}

The allocation sequence is generated by a vendor commissioned by the study sponsor. Enrolment and assignment of study participants to study intervention is done by trained study site staff; relevant user directions for the use of the IRT system are provided to each site.

## Assignment of interventions: blinding

### Who will be blinded {17a}

Study participants, investigators and clinical site staff involved in enrolment, treatment and data collection, and sponsor representatives, are blinded to study intervention. The unblinded investigational pharmacist or an appropriately qualified person responsible for the preparation of study intervention for each participant is informed via automated message from the IRT about the intervention allocation. Unblinding to the randomisation assignment is restricted to this staff only. Study documentation at the pharmacy is kept separate from other study documentation.

### Procedure for unblinding if needed {17b}

The IRT will be programmed with blind-breaking instructions. In case of an emergency, the investigator has the sole responsibility for determining if unblinding of a participant’s intervention assignment is warranted. Participant safety must always be the first consideration in making such a determination. If the investigator decides that unblinding is warranted, the investigator may, at the investigator’s discretion, contact the sponsor to discuss the situation prior to unblinding a participant’s intervention assignment unless this could delay emergency treatment for the participant.

Sponsor or sponsor delegated safety staff may unblind the intervention assignment for any participant with an SAE. If the SAE requires that an expedited regulatory report be sent to one or more regulatory agencies, a copy of the report, identifying the participant’s intervention assignment, may be sent to IRBs, REBs or IECs in accordance with local regulations.

An independent Data Safety Monitoring Committee (DSMC) will access masked or unblinded data during the study; see section Oversight and monitoring. This will have no impact on the blinding for participants, investigators and clinical site staff, or sponsor representatives.

## Data collection and management

### Plans for assessment and collection of outcomes {18a}

All data required will be recorded by trained study site staff into an electronic CRF (eCRF) accessible via an electronic data entry portal set up by a vendor delegated by the study sponsor. Access to the data entry function of the portal is limited to trained study staff who are granted individual password-protected access rights. Guidance on data entry is provided in study-specific eCRF completion guidelines.

### Plans to promote participant retention and complete follow-up {18b}

Following surgery and hospital discharge patients will be followed up at Days 60 and 90 after the first dose of study intervention. Trained study staff will keep contact with patients and remind them of attending the follow-up visits at the study site. To ease patient retention and completeness of data collection during the follow-up period these visits may be performed by qualified and trained study staff at the investigational site, at the participant's home, or other suitable location, where appropriate.

If study intervention is discontinued, the participant should still remain in the study to be evaluated for all assessments during treatment and hospital stay period as well as follow-up through to Day 90.

A participant may withdraw from the study at any time at the participant’s own request for any reason (or without providing any reason) or at the discretion of the investigator for safety reasons. At the time of discontinuing from the study, if possible and appropriate, the participant will be asked if they want to withdraw from treatment but are willing to accept continued follow up assessments. At a minimum, if appropriate, the participant should be asked if a phone call at Day 90 is acceptable to follow up on any need for RRT and possible SAEs. Where permitted by local regulations, publicly available data (eg, death records) can be included after withdrawal of consent.

### Data management {19}

Details for data entry into the eCRF, coding, security and storage of data and a description of processes related to assure data quality can be found in a separate data management plan set up by the sponsor delegate and approved by the sponsor. This plan describes the receipt and management of study data from start-up to close-out of the study. This plan also outlines the responsibilities of the applicable staff delegated by the sponsor.

### Confidentiality {27}

Participants will be assigned a unique identifier by the sponsor. Any participant records or datasets that are transferred to the sponsor will contain the identifier only; participant names or any information which would make the participant identifiable will not be transferred. The participants are informed that their personal study-related data will be used by the sponsor in accordance with local data protection law. The level of disclosure must also be explained to the participant who will be required to give consent for their data to be used as described in the ICF. Collection of personal data, also including race and ethnicity, is for scientific research purposes and in accordance with Article 89 of the General Data Protection Regulation (GDPR) and §27 of the Data Protection Adaptation and Implementation Act EU of 30 June 2017. The participant must be informed that their medical records may be examined by clinical quality assurance auditors or other authorized personnel appointed by the sponsor, by appropriate IRB/REB/IEC members, and by inspectors from regulatory authorities.

The contract between sponsor and study sites specifies responsibilities of the parties related to data protection, including handling of data security breaches and respective communication and cooperation of the parties.

Information technology systems used to collect, process, and store study-related data are secured by technical and organizational security measures designed to protect such data against accidental or unlawful loss, alteration, or unauthorized disclosure or access.

### Plans for collection, laboratory evaluation and storage of biological specimens for genetic or molecular analysis in this trial/future use {33}

There are no plans to collect, store and evaluate biological specimens for genetic or molecular analysis.

## Statistical methods

### Statistical methods for primary and secondary outcomes {20a}

Full details of the statistical methodology are described in a statistical analysis plan separate from the study protocol.

#### Primary endpoint (main analytical approach)

The eGFR change from baseline to Day 90 will be estimated using a MMRM. The change from baseline values for post baseline measurements will be modelled in the response vector and group (pooled RMC-035 and placebo), time and group*time as fixed factors. Participant will be included as a random factor in the model. The estimated difference between the pooled RMC-035 group and placebo at each time point will be calculated, along with the respective 90% confidence interval (CI) and *p*-value, where the estimated difference at the 90-day visit is defined as the primary endpoint. The estimated mean change from baseline per arm and respective 90% CI and *p*-value will also be calculated. An unstructured covariance matrix will be used to model dependence between time-points.

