#### Key secondary endpoints (man analytical approach)

Occurrence of MAKE_90_ and its components will be analysed using a Cochran-Mantel–Haenszel model to estimate of the common relative risk (pooled RMC-035 versus placebo) across the stratification group formed by eGFR at Day −1 (≥ 60 and < 60 mL/min/1.73m^2^). The estimate of the common relative risk, 90% CI utilizing Greenland and Robins, and *p*-value will be reported. The proportion of participants with MAKE_90_ and each MAKE_90_ component, and its 90% CI will be calculated.

Change from baseline in eGFR at Day 90 (by each RMC-035 dose level) will be analysed using the same model as the primary endpoint, but where treatment will include both dose levels of RMC-035 and difference versus placebo will be estimated for each dose level.

Occurrence of MAKE_90_ and its components by each RMC-035 dose level will be analysed using the same model as for the pooled treatment group analyses, but where treatment will include both dose levels of RMC-035 and relative risk versus placebo will be estimated for each dose level.

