### Methods for additional analyses (e.g. subgroup analyses) {20b}

Subgroup analyses of the primary endpoint and secondary endpoints will be performed to assess consistency of the investigational intervention effect across the following subgroups:eGFR at Screening < 60 mL/min/1.73m^2^ versus ≥ 60 mL/min/1.73 m.^2^Diabetes mellitus at Screening: Yes and NoRegion: North America and EuropeGender: Male and Female

If the number of participants is too small (less than 10%) within a subgroup, then the subgroup categories may be redefined prior to unblinding the study. The analyses will be conducted using a test for heterogeneity and results will be presented on forest plots presenting the estimated study arm difference and 90% confidence intervals.

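### The primary MMRM as written leaves out baseline eGFR and the randomisation stratum, which gives up some precision but not validity

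*Protocol article*

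**What the plan says.** Under Primary endpoint (main analytical approach), the Protocol article models post-baseline changes in eGFR with "group (pooled RMC-035 and placebo), time and group*time as fixed factors", participant as a random factor and an unstructured covariance matrix. The Day 90 contrast is the primary result. No baseline covariate is listed.

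Under Sequence generation {16a}: "Stratification for eGFR (≥ 60 and < 60 mL/min/1.73m^2^) will be implemented", with at least 30% of participants in the lower stratum.

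The section on key secondary endpoints treats its two outcomes differently. MAKE at Day 90 uses a Cochran-Mantel-Haenszel analysis "to estimate of the common relative risk (pooled RMC-035 versus placebo) across the stratification group formed by eGFR" at Day −1. The by-dose eGFR analysis takes over the primary model, with the two doses as separate groups.

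The sensitivity analyses of the primary endpoint also reuse that model. One adds exposure to SGLT2 inhibitors, ACE inhibitors or ARBs; two replace creatinine-based eGFR by versions that use cystatin C. None adds baseline eGFR or the stratum.

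**The concern.** Change from baseline is usually correlated with baseline, partly through regression to the mean. Here there is a further reason. Eligibility runs from an eGFR of 30 upward with no ceiling, and the trial's own MAKE definition counts a relative loss of 25%. That is 7.5 mL/min/1.73m² at an eGFR of 30 (0.25 × 30) and 22.5 at 90 (0.25 × 90). Absolute loss may well depend on the starting value. Analysing change scores does not remove that dependence, and because the response vector holds only post-baseline changes, baseline does not enter the model by another route.

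Two things would be at stake. First, variance that baseline eGFR could explain stays in the residual, so the standard error of the Day 90 difference is larger than it need be. Second, stratified randomisation balances the arms on the stratum, but a model without the stratum does not take credit for that balance. Its standard error then overstates the real variability of the estimate. The by-dose comparisons, which inform dose choice, inherit both effects. The plan already follows the principle for MAKE at Day 90, so the primary analysis is out of step with the rest of the plan.

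**Working it through.** **1. The plan's own figure.** Inputs from Sample size {14}: target power 80%; level 10%, two-sided; difference and SD as planned ("assuming a treatment effect of 5 mL/min/1.73m^2^ and a standard deviation of 12 mL/min/1.73m^2"); arms of "46 for RMC-035 low dose, 46 for RMC-035 high dose, and 69 for placebo". That is 92 pooled against 69, with k = 92/69 = 4/3. The stated losses are 10% drop-out and 5% information loss.

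Evaluable N = (1 + 1/k)(1 + k) × [12 × (1.645 + 0.842)/5]² = 4.083 × 35.61 = 145.4. Dividing by 0.90 gives 161.6, which matches 161.

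Power = Φ(5/SE − 1.645), with SE = 12 × √(1/(69f) + 1/(92f)) and f the fraction retained:

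| Loss applied | f | Power |
|---|---|---|
| none | 1 | 83.4% |
| 5% | 0.95 | 81.7% |
| 10% | 0.90 | 79.9% |
| 10% and 5% multiplied | 0.855 | 78.1% |

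The planned number therefore reproduces with the 10% loss alone.

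**2. Gain from adjustment.** Let r be the correlation of Day 90 change with baseline eGFR. The document does not give it, so the values below are assumed. The residual SD becomes 12 × √(1 − r²). With f = 0.855 (about 59 and 78.7 evaluable):

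| assumed r (absolute) | residual SD | SE | Power | N randomised for 80% |
|---|---|---|---|---|
| 0 | 12.00 | 2.07 | 78.1% | 171 |
| 0.1 | 11.94 | 2.06 | 78.4% | 169 |
| 0.2 | 11.76 | 2.02 | 79.5% | 164 |
| 0.3 | 11.45 | 1.97 | 81.4% | 155 |
| 0.4 | 11.00 | 1.89 | 84.0% | 143 |

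A correlation of about 0.23 would bring power to 80% at 161 with both losses multiplied.

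**3. What stratified randomisation already delivers.** The table above holds the unadjusted power at 78.1% for every r. That is too low when part of the correlation acts through a balanced stratum. Suppose a share q = 0.30 lies in the lower stratum and mean change differs between strata by d (assumed), with total SD 12. The stratum then explains R² = q(1 − q)d²/144. The unadjusted test's actual level is 2 × [1 − Φ(1.645/√(1 − R²))]:

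- d = 5: R² = 0.21 × 25/144 = 0.036, level about 9.4%.
- d = 8: R² = 0.21 × 64/144 = 0.093, level about 8.4%.

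A simulation (20,000 replicates, 59 against 79 evaluable, strata balanced, true difference 0 or 5) gave:

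| assumed d | Type I error, unadjusted | Type I error, stratum in model | Power, unadjusted | Power, stratum in model |
|---|---|---|---|---|
| 0 | 10.0% | 10.0% | 78.5% | 78.5% |
| 4 | 9.6% | 10.0% | 78.7% | 79.3% |
| 8 | 8.4% | 10.0% | 79.3% | 81.6% |
| 12 | 6.5% | 10.0% | 80.6% | 86.1% |

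At d = 8 (equivalent to r = √0.093 = 0.31) the total gain over d = 0 is 81.6 − 78.5 = 3.1 points. Of that, 79.3 − 78.5 = 0.8 comes from the design and 81.6 − 79.3 = 2.3 from the model term. The mean standard error is 2.062 unadjusted and 1.961 adjusted, so the unadjusted 90% interval is about 5% wider than needed (2.062/1.961 = 1.05).

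**The case against.** The strongest reply is that this concerns efficiency only. Randomisation protects the comparison, and the unadjusted test errs on the conservative side, so no false positive can arise from the omission. That stands. A reader might infer that the primary result would be biased or invalid; the document does not support that.

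The article refers to a separate statistical analysis plan for full details, and covariates are often listed there. This limits what can be said about the trial as it will be analysed. It does not remove the point, because the article does name the fixed effects of the primary model and the list is incomplete.

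Chance imbalance in baseline eGFR is a weaker worry than it looks. Stratifying at 60 limits gross imbalance, and only imbalance within strata remains.

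A reader might also infer that the trial is underpowered without adjustment. The sample size section does not say how the two losses combine. The 78.1% arises only if they are multiplied; with the 10% loss alone, power is 79.9%. An MMRM also uses earlier visits of participants who miss Day 90.

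Finally, the subgroup definition "eGFR at Screening < 60 mL/min/1.73m^2^ versus ≥ 60" may suggest that a different eGFR value is used there. That cannot be established: Day −1, the day of randomisation and of the first baseline creatinine, lies inside the screening period in Participant timeline {13}. The analysis of MAKE at Day 90 already uses the stratification group at Day −1, so it needs no correction.

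**Conclusion.** The point holds as a matter of precision. The published primary MMRM and its by-dose and cystatin C versions omit a baseline measurement that the trial collects and a factor that it randomises by. The consequence is a somewhat larger standard error and, if the stratum is prognostic, a test that runs below its nominal 10%.

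The size depends on two quantities that the document does not give. At an assumed absolute correlation of 0.1 the gain is about 0.3 power points (78.1% to 78.4%) and hardly matters. At 0.4 it is about 6 points (to 84.0%), less what stratified randomisation already provides. For assumed stratum differences of 5 and 8 mL/min/1.73m², the actual level is about 9.4% and 8.4%. The power figures assume an SD of 12, a difference of 5 and both losses multiplied.

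This is a worthwhile improvement rather than an error that threatens the conclusion.

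**What to change.** Before unblinding, add three fixed effects to the primary, by-dose and cystatin C MMRMs: continuous baseline eGFR (the mean of the duplicate baseline values, calculated with the same equation as the response), baseline-by-time, and the eGFR stratum as randomised. Keep the present unadjusted model as a sensitivity analysis. If the separate analysis plan already includes these terms, it is enough to align the published description with it.

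No new data are needed, but the change is not entirely free. Trial status reports that enrolment ended on June 03, 2025, so the primary model would be altered late, and the amendment should be dated and shown to precede unblinding. The document does not say whether unblinding has taken place. If it has, the stated model should stay primary and the adjusted one be reported as supplementary. Continuous baseline eGFR and the dichotomised stratum also overlap, so the second term may add little to the first; the cost is a few degrees of freedom with about 138 evaluable participants (161 × 0.855).

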RMC-035 has also been evaluated in clinical trials, including the phase 2 AKITA trial, which enrolled cardiac surgery patients at increased risk for AKI. Notably, RMC-035 improved kidney-related secondary outcomes compared to placebo, including estimated glomerular filtration rate (eGFR) and major adverse kidney events at Day 90 (MAKE_90_). Although the primary outcome – AKI within 72 h after surgery – was not met, the analysis was confounded by a short-term, reversible increase in SCr at the highest RMC-035 dose/exposure levels. This finding aligns with toxicological evaluations demonstrating kidney tubular protein overload when exceeding the maximum tubular capacity for RMC-035 uptake [8].

To optimize the benefit-risk profile of RMC-035 before a pivotal Phase 3 trial, a Phase 2b dose-optimization trial is underway, with key design elements presented herein. This clinical trial [NCT06475274; EU CT number 2024–510658-28] aims to evaluate the efficacy of RMC-035 at two different dosage strengths, focusing on its impact on long-term kidney function in cardiac surgery patients at increased risk for AKI.

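### The primary MMRM pools the two doses into one group and the dose effects come from a separate fit, so the primary estimate need not equal the average dose effect if time course and retention both differ by dose

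*Protocol article*

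**What the plan says.** Under the main analytical approach for the primary endpoint, the article fits an MMRM to change from baseline in eGFR with "group (pooled RMC-035 and placebo), time and group*time as fixed factors". It takes the pooled-minus-placebo difference from this fit, "where the estimated difference at the 90-day visit is defined as the primary endpoint". On the covariance it says: "An unstructured covariance matrix will be used to model dependence between time-points".

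For the dose-level Day 90 effects, the key secondary section uses the same model, "but where treatment will include both dose levels of RMC-035 and difference versus placebo will be estimated for each dose level". That is a second fit with three treatment levels. The article does not define the pooled effect as a contrast from the three-arm model, and it does not say how the doses are weighted.

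Three other places bear on this:

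- **Sample size:** arms of "46 for RMC-035 low dose, 46 for RMC-035 high dose, and 69 for placebo", with a single drop-out figure of 10% and none by dose.
- **Missing data (item 20c):** the MMRM is also the means of carrying out the treatment policy strategy for eGFR change.
- **Background:** of the earlier trial's primary outcome, the article says that "the analysis was confounded by a short-term, reversible increase in SCr at the highest RMC-035 dose/exposure levels".

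**The concern.** An MMRM handles a missing Day 90 value through the participant's earlier values, judged against the modelled mean of that participant's group. In the two-level model, that mean is a mixture of two doses. Two things follow when retention differs by dose.

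1. The pooled Day 90 mean leans towards the dose that kept more participants, although the doses were randomised equally.
2. If one dose has a temporary early fall in eGFR, its participants sit below the mixed early mean. The model treats that drug effect as individual prognosis and carries part of it into Day 90.

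The second point matters here because Day 90 was chosen so that perioperative effects would not drive the result. The trial's purpose is dose selection, so readers will set the pooled result beside the two dose results. A pooled figure that is not their average would need explaining.

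**Working it through.** **The plan's own figure.** The article plans "at least 80% power to detect a significant effect of pooled dose levels compared to placebo at a 10% two-sided significance level". Its inputs are a difference of 5 and an SD of 12 mL/min/1.73m^2. With 10% drop-out, 69 × 0.9 = 62.1 placebo and 92 × 0.9 = 82.8 pooled participants remain.

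SE = 12 × √(1/62.1 + 1/82.8) = 2.014, and power = Φ(5/2.014 − 1.645) = 79.9%. The required total is 145.4/0.9 = 161.6, so 161 is reproduced on the 10% drop-out alone.

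**Assumptions (none is in the article).** Day 90 retention by dose; Day 90 effects by dose (30 mg/60 mg) averaging 5; an early eGFR shift of −8 at 60 mg; early-to-Day-90 correlation 0.5; SD 12 at each visit; placebo retention 90%; Day 60 and Day 90 missing together.

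**Formula.** Let w30 and w60 be each dose's share of retained pooled participants, and f the pooled share of all retained participants. Let d30 and d60 be the Day 90 effects and e the early shift at 60 mg. In large samples the two-level estimate minus the average dose effect is

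(w30·d30 + w60·d60 − (d30 + d60)/2) + b × (0.5·e − w60·e),

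where b = (72 + f·w30·w60·e·(d60 − d30)) / (144 + f·w30·w60·e²), and 72 = 0.5 × 12².

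**Effects 3/7, retention 95/85%.**
- Retained: 43.7 and 39.1, so w30 = 0.5278 and f = 82.8/144.9 = 0.571.
- Weighting term: 0.5278 × 3 + 0.4722 × 7 − 5 = −0.111.
- b = (72 − 4.56)/(144 + 9.11) = 0.4405.
- Early term: 0.4405 × (−4 + 3.778) = −0.098.
- Total: **−0.21**.

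| Effects 30/60 mg | Early shift | Retention 30/60 mg | Shift |
|---|---|---|---|
| any | any | 90/90% | 0.00 |
| 5/5 | none | any | 0.00 |
| 3/7 | −8 | 95/85% | −0.21 |
| 3/7 | −8 | 95/80% | −0.32 |
| 5/5 | −8 | 95/85% | −0.10 |
| 5/5 | −8 | 95/80% | −0.16 |
| 7/3 | −8 | 95/85% | 0.00 (the terms cancel) |
| 7/3 | none | 95/85% | +0.11 |
| 3/7 | −8 | 85/95% | +0.21 |

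Simulated trials of 46/46/69 under similar assumptions gave −0.21 and −0.33 for rows three and four. With drop-out driven by the 72 h eGFR they gave −0.05 (5/5) and −0.10 (3/7).

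**If only Day 90 is missing.** With Day 60 observed and correlated 0.85 with Day 90, the 3/7 shifts fall to about −0.04 (95/85%) and −0.06 to −0.07 (95/80%).

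**Against the SE.** At 95/80% retention the SE is 12 × √(1/62.1 + 1/80.5) = 2.03, so 0.32 is 0.16 SE. The largest shift over a wider grid was 0.62 (effects 2/8, shift −10, correlation 0.8, a 20-point gap).

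**No Day 90 effect.** With no dose effect at any visit, both models target zero. With an early shift of −8 but no Day 90 effect, the two-level estimate centres on −0.10 (95/85%) or −0.16 (95/80%). The two-sided 10% test then rejects 10.0% or 10.1% of the time.

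**Cost of the equal-weight contrast.** SE = 12 × √(1/n0 + (1/n30 + 1/n60)/4), where n0, n30 and n60 are the retained numbers on placebo, 30 mg and 60 mg.

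| Retention 30/60 mg | SE contrast | SE two-level | Power contrast | Power two-level (5/5, no early shift) |
|---|---|---|---|---|
| 90/90% | 2.014 | 2.014 | 79.9% | 79.9% |
| 95/85% | 2.016 | 2.014 | 79.8% | 79.9% |
| 95/75% | 2.046 | 2.040 | 78.8% | 79.0% |

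**The case against.** The strongest reply is that the model matches the objective. The trial asks whether pooled RMC-035 beats placebo, it is powered for that, and nothing in the article names an equal-weight average as the target. This is partly right: with equal retention the two-level model delivers that average. It does not cover the rows with effects 5/5. There both doses have the same Day 90 effect, so no choice of weights explains a pooled estimate below 5.

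The second reply is that the harm needs two conditions together and the article documents neither. This stands. Participants who stop study drug are followed to Day 90, home visits are allowed, and dosing ends at 24 h, all of which should limit a retention gap. A reader might infer that the article predicts an early creatinine rise at 60 mg. It does not: the background describes the highest exposures in the earlier trial, and the discussion says the regimen has since been changed. An early shift here is plausible, not established.

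The third reply is that the direction is open. This also stands. A reader might infer a built-in loss of 4 to 5 points of power. That figure belongs to one cell: a 15-point gap, both late visits lost, and the better dose losing more participants. Reversing the gap reverses the sign.

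The SAP, which is not shown, could define the contrast. The point is about the two-level factor that the article does state.

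**Conclusion.** The point holds as a minor refinement. As written, the primary and dose-level results come from two fits that agree in expectation unless the doses differ in both time course and retention. When both differ, a retention gap of 10 to 15 points moves the primary estimate by about 0 to 0.3 mL/min/1.73m^2 either way, roughly 0.15 SE at most in these scenarios. The shift is well below 0.1 if Day 60 is observed. These sizes rest on assumed retention, dose effects, early shift and correlations.

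It would be wrong to conclude that the primary test is invalid or that the estimate is biased in a known direction. Even with an early shift and no Day 90 effect, the error rate barely moves from 10%. What is at stake is a clear meaning for the pooled estimate and its agreement with the dose results.

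**What to change.** Before unblinding, specify one MMRM with the three randomised arms, time and arm-by-time. Define the primary estimate as the Day 90 contrast 0.5 × (30 mg) + 0.5 × (60 mg) − placebo, tested at the same two-sided 10% level. Take both dose-level differences from that fit, so that the pooled result is their average by construction.

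The cost is one more mean parameter per visit and at most about 0.2 points of power, with no new data. If the SAP already defines this contrast, only the protocol wording needs aligning. If not, the change is a sentence in each document, and any protocol amendment goes through the approvals the article describes.
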